#### Outcomes

The primary outcome will be the comparison of the NL-IHRS between the two branches of the study after 24 months.

The secondary outcomes after 24 months will be quality of life, as assessed by the WHOQOL-BREF [17], modification of diet, according to the DASH questionnaire [18], modification of physical activity, following the IPAQ-short [19], BMI reduction, smoking level, modification of self-declared alcohol consumption.
The WHOQOL-BREF questionnaire was derived from the WHOQOL-100 in 1996 to assess quality of life by using thirty-three questions within the four following domains: physical health, psychological domain, social relationships and environment.The DASH questionnaire was created in 2016 to assess, by means of eleven questions, the quality of an individual’s diet, according to the Dietary Approach to Stop Hypertension. This diet was designed along the lines of the Mediterranean diet to improve the cardiovascular risk profile of the consumers [20].The IPAQ was created in 2003 to assess physical activity. The short version comprises seven questions in four blocks which describe intense activity, moderate activity, walking in the last 7 days and time spent seated. The score of the IPAQ-short can be converted in Metabolic Equivalents of Task, a standardised measurement of physical activity level.

The tertiary outcomes will be the same as previously stated, assessed at 6 and 12 months. The implementation strategy will be assessed by mixed methods comprising qualitative research methods and quantitative descriptive epidemiological studies [21]. Quantitative implementation data collected at 12 and 24 months will consist of the number of people screened with the NL-IHRS, the number of people entering the behavioural change intervention, the number of people completing the entire intervention, the cost of the intervention. Qualitative studies will be constructed using the Re-Aim model [22], exploring invention barriers and facilitators and perspectives from screeners, community champions, stakeholders and members of the research team.

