#### Sample size

The primary outcome will be analysed with intention-to-treat. An inter-group comparative analysis will be performed at the end of the intervention on the primary outcome. A difference in the mean NL-IHRS of 15% is expected between the intervention and the control groups. Secondary outcomes at 24 months will consist of differences in scores for quality of life (WHOQUOL-BREF), DASH questionnaire, IPAQ-short, reported smoking status, reported alcohol consumption. Tertiary outcomes, at 6- and 12-months, will consist of differences in the NL-IHRS, WHOQUOL-BREF, DASH questionnaire results, as well as the IPAQ-short, the reported smoking status and the reported alcohol consumption results.

The implementation outcomes will be the number of participants entering the groups, the number of people following the entire intervention (attendance at 75% or more of the group meetings), and the cost of the intervention.

Randomisation will be applied automatically by Redcap©.

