### Statistical methods

For stage 1, a descriptive epidemiological analysis will be carried out on the screened population. The total number of screenings, the distribution of the population within low-, intermediate- and high-cardiovascular risk scores, and the frequency of the modifiable risk factors listed in the score will be described.

For stage 2, the calculation of the number of subjects required is based on the comparison of the mean NL-IHRS between the two branches of the study: for a power of 80%, an alpha risk = 0.05 and an effect size (mean difference / standard deviation) of 0.20, the number of subjects required is 394 per branch. The figure of 985 subjects, including about 20% potentially lost to follow-up, should be included in the total. With the number of subjects being 394 patients per branch and the hypothesis of an effect size of 0.20 for each secondary endpoint, the test power is approximately 68% for each secondary endpoint using the Holm-Bonferroni correction to allow for multiple comparisons.

The analysis of the RCT will be conducted on an “intention to treat” basis.

No intermediate analysis will be conducted because this study leads to no biomedical risk.

A hierarchical analysis will be conducted in two steps. First, a comparison of the mean NL-IHRS between the two branches at alpha risk = 0.05 then, in the event of a statistically significant result, a comparison of the 6 secondary endpoints between the two branches, using the Holm-Bonferroni correction to consider the multiple comparisons made at this stage. In accordance with the principles of hierarchical analysis, the tests provided for in the second step will only be carried out in a demonstrative manner if the test performed in the first step is statistically significant (*p* < 0.05).

The quantitative outcomes will be compared between the two branches using a Student test. The qualitative endpoints will be compared between the two groups using a Chi-square test. Secondary, multivariate analyses will be performed using a linear model to adjust for potential confounding factors.

Missing data will be identified via the electronic CRF, and investigators will be called back to complete the data. The remaining incomplete files will be declared as lost to follow-up.

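### Declaring every incomplete file lost to follow-up would, read as written, turn the declared intention-to-treat analysis into a complete-file analysis

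*Protocol article*

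**What the plan says.** The protocol article commits to intention to treat in two sections. Under Sample size: "The primary outcome will be analysed with intention-to-treat". Under Statistical methods: "The analysis of the RCT will be conducted on an “intention to treat” basis".

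The Statistical methods section then deals with missing data in two sentences. The first is a query step: "Missing data will be identified via the electronic CRF, and investigators will be called back to complete the data". The second settles what is left: "The remaining incomplete files will be declared as lost to follow-up". The article names no other handling of missing data. The test for the primary outcome follows from "The quantitative outcomes will be compared between the two branches using a Student test".

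The same section sizes the trial "for a power of 80%, an alpha risk = 0.05 and an effect size (mean difference / standard deviation) of 0.20", which it says needs 394 per branch, and adds: "The figure of 985 subjects, including about 20% potentially lost to follow-up, should be included in the total".

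The Outcomes section sets the primary comparison at 24 months. It lists six secondary outcomes at that time: WHOQOL-BREF, DASH, IPAQ-short, BMI, smoking and alcohol. It then states: "The tertiary outcomes will be the same as previously stated, assessed at 6 and 12 months". The Sample size section confirms that these earlier assessments include the NL-IHRS.

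**The concern.** The rule acts on the file, not on the outcome being analysed. Nothing limits an incomplete file to one that lacks the 24-month NL-IHRS. A participant who has that score but left the WHOQOL-BREF, DASH or IPAQ-short unfinished would, on a plain reading, be reclassified as lost.

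Two things are at stake. The first is power, because observed primary outcomes would be discarded. The second is validity, because a comparison restricted to complete files is no longer protected by randomisation if the reasons for incompleteness relate to the score and act differently in the two arms.

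The article gives some grounds to take the second seriously. Only the intervention arm is asked to attend 13 group meetings over two years (Stage 2: RCT). The Discussion notes that relapse often comes 6 months to 1 year after a change begins, which is before the 24-month endpoint. The planned effect is small at 0.20 SD, so even a modest bias would matter. A false-positive primary result would also open the second step of the hierarchical analysis, with its six secondary tests.

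**Working it through.** **Inputs from the article.** Effect size 0.20, alpha 0.05 (taken as two-sided, which reproduces the plan), power 80%, 394 per branch, 985 in total, about 20% potential loss (Statistical methods); equal randomisation (Abstract).

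**1. The plan's own figures.**
- Number per arm for two means with d = 0.20: 393 by normal approximation; 393.4, rounded up to 394, by the t test. Power at 394 per arm is 80.2%. The stated 394 reproduces.
- Total: 2 × 394 = 788, and 788 / 0.80 = 985. The stated 985 reproduces exactly.
- Secondary power by simulation of Holm's procedure, six endpoints, d = 0.20, 394 per arm: 68.6% if the endpoints are independent, 67.8% at correlation 0.3. The stated 68% or so reproduces.

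The sample size is therefore correct. Both power statements are made at 394 per branch, the number left after the allowance for loss. So the calculation does not count on any contribution from those lost.

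**2. Is exclusion the natural reading?** Three facts point the same way: the only stated rule reclassifies the whole file as lost; the Student test uses observed values only; and the power figures rest on the post-loss number. None of them states exclusion outright.

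**3. Power cost if the rule removes retained files.** The share removed, x, is an assumption. Number per arm = 394 × (1 − x).

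| x | per arm | power |
|---|---|---|
| 0 | 394 | 80.2% |
| 5% | 374 | 78.1% |
| 10% | 355 | 75.9% |

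**4. Bias.** Let d be the share lost in an arm and g the gap, in SD, by which lost participants score worse (higher) than those retained. The retained mean understates the arm mean by d × g. The bias in the contrast is d1·g1 − d0·g0 (1 = intervention, 0 = control); a positive value flatters the intervention. Every d and g below is an assumption. Type I error uses 492.5 × (1 − d) per arm.

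| loss, intervention vs control | gap g | bias (SD) | share of 0.20 | two-sided type I error |
|---|---|---|---|---|
| 20% vs 20% | 0.2 to 0.5, same in both arms | 0 | 0% | 5.0% |
| 25% vs 15% | 0.2 to 0.5 | 0.02 to 0.05 | 10 to 25% | 5.9 to 10.8% |
| 30% vs 10% | 0.2 to 0.5 | 0.04 to 0.10 | 20 to 50% | 8.6 to 28.6% |

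Example: 0.25 × 0.5 − 0.15 × 0.5 = 0.05 SD.

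Equal loss is not sufficient for zero bias. With 20% lost in each arm and a gap of 0.3 to 0.5 SD in the intervention arm only, the bias is 0.20 × 0.3 = 0.06 to 0.20 × 0.5 = 0.10 SD.

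**The case against.** The strongest reply is that the article never says participants declared lost are dropped from the analysis. It also leaves the word file undefined: this could mean the visit record or the record for the outcome being tested. Someone with no 24-month value is a missing-data problem under any intention-to-treat plan, and the choice of imputation or model is commonly left to a statistical analysis plan, which is not shown here. This stands in part. Exclusion is an inference, and a flat contradiction of intention to treat would arise only for people whose 24-month NL-IHRS is observed and then set aside. But the point concerns a rule that the article states, not a detail it omits, and a later plan that kept these participants would have to override or clarify that sentence.

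Three stronger readings are tempting, and the documents do not support them:
- **That the plan intends to exclude 197 people.** 985 − 788 = 197, but dividing by 0.80 is routine protection of power, and the article speaks of potential loss. It is not a definition of the analysis set.
- **That retention will differ by arm.** Both arms receive brief advice every 6 months and are assessed on the same outcomes at the same times. Missing a group meeting is not missing an outcome assessment; attendance is tracked separately as an implementation outcome. Differential loss is plausible, not shown.
- **That incomplete questionnaires necessarily come off the 788.** Files declared lost belong to the category that the 20% allowance covers, so they may already be counted there.

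Comparing the arms at 24 months with a t test is also a legitimate design choice in itself. The case for a longitudinal model rests on the missing data, not on any error in choosing that test.

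**Conclusion.** The point holds as a defect in a stated rule. Followed literally, it replaces the declared intention-to-treat analysis with one of complete files and can discard observed primary outcomes. The sample-size arithmetic is sound, but the 20% allowance protects power and not validity.

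The power cost is small: from about 80% to 78 to 76% if a further 5 to 10% of retained files were removed, and less if those files already fall within the allowance. The bias could matter more, at 0.02 to 0.10 SD under the differential-loss patterns examined. Those figures rest wholly on assumed loss splits and score gaps, and the bias is zero if loss and its relation to outcome match across arms. A reader should not conclude that the trial will be biased, only that the rule leaves it exposed and that the article names no analysis to examine this.

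**What to change.** Under Statistical methods, replace the file-level rule with missingness defined outcome by outcome. State that every observed 24-month NL-IHRS is analysed in the allocated arm, whatever else in the record is missing.

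Estimate the 24-month contrast in all randomised participants with a repeated-measures model using the baseline, 6-, 12- and 24-month NL-IHRS, and amend the sentence naming the Student test for the primary outcome accordingly. Add a delta-adjusted sensitivity analysis with separate shifts for each arm, and report loss by arm.

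The cost is revised wording and modest extra programming; the measurements are already scheduled. The main analysis would then rely on data being missing at random, which is itself an assumption; the sensitivity analysis is there to probe it.

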### Methods: monitoring

Data monitoring will be overseen by a monitoring committee independent of the sponsors from the CHRU Brest. This will take place at each 6-monthly stage.

### Ethics and dissemination

Ethics approval was obtained from the national French ethics committee. Informed consent will be written for each participant, community champion, screener and researcher.

The final dataset will be hosted via Redcap at The University of Antwerp. The access to the final dataset will be granted by requiring it to the investigators. There is no contractual agreement that limits access to the dataset. A publication policy was designed by the SPICES consortium comprising a project logo, international and national websites, newspapers articles, newsletters, conferences, videos addressed to study participants, stakeholders, and general population.

## Discussion

The aim of this study is to assess an innovative prevention strategy for cardiovascular diseases. If the NL-IHRS is improved, this can provide an argument in favour of reorganising healthcare policies in high-income countries. A substantial change would be to relocate primary prevention from healthcare professionals to lay people and to the community.

If the NL-IHRS is not improved, new hypotheses should be tested. Current evaluation of prevention shows that healthcare professional-led individual cardiovascular primary prevention is not effective. If community-led individual cardiovascular primary prevention targeting behavioural change is not effective either, then public health institutions should readdress budgets directed towards other strategies. Other individual strategies that have been tested include food labelling and economic incentives to promote healthy diet [5]. Public policies that could be effective include public space adaptation, such as the development of pedestrian paths or cycle paths to promote regular physical activity [23].

Secondary aims would be to assess the efficacy of Motivational Interviewing by a RCT which would provide evidence at Level II. Evidence of effectiveness of Motivational Interviewing is still scarce [24]. If Motivational Interviewing is assessed and shown to be effective in this study, it should advocate extensive training among both healthcare professionals and lay people. Group dynamics is also evaluated in this study. A successful outcome would contribute to the upgrading of recommendations edited by national and international guidelines which are scarce and currently supported by a poor level of evidence.

The efficacy of brief advice by professionals is already established for smoking cessation [25]. This study will demonstrate the feasibility of delivering cardiovascular-related brief advice on a large scale.

Additionally, the effectiveness of community champions on cardiovascular prevention will be tested in a high-income country. Initially, the use of community champions was promoted and proved effective in the prevention and treatment of HIV in Sub Saharan countries [26]. The WHO recommends relying on patients’ families and communities when dealing with the burden of chronic diseases [27]. The success of the champions-led intervention would advocate a commitment to involving lay people in cardiovascular prevention. This commitment is both cost-effective and could be disseminated rapidly, compared with the recruitment and training of healthcare professionals. Healthcare costs are a current issue across the board, from low-income countries to high-income countries.

The objectives of this study are ambitious, especially as regards the study duration. A current challenge in changing behaviours and lifestyle habits is the possibility of relapse. Relapse often occurs 6 months to 1 year after the initiation of the change. A two-year duration will produce stronger proof of efficacy. Moreover, many studies did not assess the improvement of cardiovascular risk, as this study will do, only levels of readiness to change, activation of behavioural change or health awareness.

The implementation provides documented understanding about the effectiveness of the intervention and about what works, or does not work, in a peculiar type of setting. The research team chose internationally acknowledged models to structure implementation, such as Re-Aim and CFIR [28, 29]. Implementation tools will be regularly discussed and chosen by consensus within the international team. This study will provide valuable data for future research or prevention implementations, in practical barriers and facilitators related to large population screening and community-led primary prevention. Current French evaluation mainly focuses on barriers to information diffusion on a national scale. This study will demonstrate that the collective involvement of local elected representatives, researchers and local volunteers enables primary prevention programs on a regional scale.

Each country of the SPICES consortium will adapt non-pharmacological cardiovascular prevention interventions to its setting, will evaluate and monitor its progress, using community reinforcement, community champions and community health workers. Data from the French setting will be compared with data from the other SPICES settings, providing an international overview of community-led primary prevention strategies.

## Data Availability

Not applicable.

## Abbreviations

RCT: Randomized controlled trial
SPICES: Scaling-up packages of interventions for cardiovascular disease prevention in selected sites in Europe and Sub-saharan Africa
CVD: Cardiovascular disease
COB: Pays centre ouest bretagne
NL-IHRS: Non-laboratory INTERHEART score
BMI: Body mass index
WHO: World health organization
SPIRIT: Standard protocol items: recommendations for interventional trials
re-aim: Reach, effectiveness, adoption, implementation, and maintenance
CFIR: Consolidated framework for implementation research
